**Figure 1 F1:**
[figure not shown]
**Schematic drawing of the patch containing four electrodes in a diamond shaped pattern plus a ground electrode.** The patch is placed just underneath the umbilicus in the midline of the maternal abdomen. A reference electrode is placed on the left anterior superior iliac spine.

#### EHG signal analysis

All signal processing and analysis will be performed afterwards offline without knowledge of the pregnancy outcome. Identifying the CV vector will consist of three steps: selection of the contraction segments, estimating the time delays between the channels and calculating the CV vector, see Figure 2. The automatic selection of contractions will be based on the estimate of the internal uterine pressure (eIUP) which is derived from the EHG signal [18]. The algorithm used for the eIUP, as well as the algorithm used for detection of onset and duration of contractions, will be adapted to be suitable for the unpredictable nature of premature and non-labor contractions. Prior to the CV analysis, visual review of the signals will be used to optimize the automatic burst selection.

**Figure 2 F2:**
[figure not shown]
**The method for analyzing the EHG CV.** The EHG is recorded using a fixed configuration of four electrodes plus ground and reference electrodes. The eIUP is derived from the EHG signal and is used for selecting contraction segments. Finally, the delays are estimated in overlapping windows using cross-correlation.

In the signal segments selected as contractions, the CV will be determined in overlapping windows. The length of these windows will be fixed to a value to allow single spikes to be included. Cross-correlation will be used for estimation of the time delay between channels. We will describe the EHG propagation by a CV vector. This CV vector has an amplitude and an incidence angle with respect to the vertical axis. Based on statistical analysis, a threshold value will be determined for the CV vector amplitude. Values above this threshold will be considered to be artefacts and discarded.

### Study parameters/Endpoints

Patients will be classified as labor group and non-labor group based on the interval between measurement and delivery. The cutoff points will be delivery within 1, 2, 7, and 14 days of the measurement. As primary outcome the EHG parameters will be compared between these groups in terms of amplitude and angle of the CV. In order to be independent of the number of analyzed segments and contractions per patient, the average CV vector will be identified for each analyzed contraction and subsequently the average CV vector for each patient will be determined. As secondary analysis the TVU CL will be compared between the labor and non-labor group. The sensitivity and specificity will be calculated for the EHG parameters and TVU CL for predicting preterm delivery within 1, 2, 7, and 14 days. In order to be independent on arbitrarily chosen cutoff points, the area under the curve of the receiver operating characteristics will be determined.

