**Methods/Design:**

The study design will be an observational cohort study. 100 pregnant women, gestational age between 23 + 5 and 34 weeks, admitted for threatening preterm labor or preterm prelabor rupture of membranes, will be included. The length of the cervical canal will be measured by transvaginal ultrasound. The EHG will be recorded using 4 electrodes in a fixed configuration. Contractions will be detected by analysis of the EHG and using an estimation of the intra uterine pressure. In the selected contractions, the delays between channels will be estimated by cross-correlation, and subsequently, the average EHG conduction velocity will be derived. Patients will be classified as labor group and non-labor group based on the time between measurement and delivery. The average conduction velocity and cervical length will be compared between the groups. The main study endpoints will be sensitivity, specificity, and area under the ROC curve for delivery within 1,2,4,7, and 14 days from the measurement.

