### Sample size

During the year 2010, a total of 150 patients were admitted to the obstetrical ward of the Máxima Medical Center for threatening preterm labor which met the inclusion criteria. Approximately 40% of these patients delivered within 7 days. A sample size can be calculated based on an observed difference in test characteristics between the standard diagnostics and the EHG analysis using a fixed allocation ratio of 40 – 60% for the positive and negative group respectively. In the study by Lucovnik et al. an area under the curve of the receiver operating characteristics (ROC) of 0,96 was observed for the EHG analysis and 0,72 for the Bishop score (the best performing test among the standard diagnostics) [5].

A sample of 7 from the positive group and 11 from the negative group achieve 82% power, assuming an area under the ROC curve of 0,95 for EHG CV analysis and 0,70 for the standard diagnostics and using a two-sided *z*-test at a significance level of 0.05. This means a minimal number of 20 patients will need to be included. However, this observed difference is based on a single study. In order to increase the likelihood of detecting a difference in case of a lower observed difference or different allocation ratio, we propose to include a total of 100 patients.

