### Statistical analysis

Baseline characteristics will be determined for the labor and non-labor group. Differences will be tested for statistical significance using a fisher exact test for dichotomized variables and a non-paired *t*-test for continuous variables. We will evaluate the influence of significant differences in background variables on the outcome using a multivariate logistical regression model.

The Shapiro–Wilk test will be applied to test for a normal distribution of the estimated values of the CV vector amplitude. Levene’s test will be applied to test for equal variances in the labor and non-labor group. An independent samples t-test will be used to test for a significant difference in amplitude of the CV between both groups. The alpha will be set to 0.05 for all statistical tests. Using contingency tables, the sensitivity and specificity of the EHG and standard diagnostics will be determined.

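### The primary comparison is made at four delivery windows with no lead window and 0.05 for every test, so the primary false-positive rate is about 10–16% for CV amplitude alone; the main endpoint and the list of windows also differ between sections

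*Protocol article*

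**What the plan says.** Under Study parameters/Endpoints, women are split into labor and non-labor groups by the interval from measurement to delivery: "The cutoff points will be delivery within 1, 2, 7, and 14 days of the measurement". The next sentence fixes the primary outcome: "As primary outcome the EHG parameters will be compared between these groups in terms of amplitude and angle of the CV". The groups meant are the splits at all four windows, and none is singled out.

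The Statistical analysis section gives a single rule for significance: "The alpha will be set to 0.05 for all statistical tests". It names a test for one of the two parameters: "An independent samples t-test will be used to test for a significant difference in amplitude of the CV between both groups". It names none for angle.

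Two other sections describe the main analysis differently:

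- The Abstract (Methods/Design) lists sensitivity, specificity and "area under the ROC curve for delivery within 1,2,4,7, and 14 days from the measurement" as the main endpoints. That is five windows, including a 4-day one that appears neither in the endpoint section nor in the Discussion.
- The Sample size section powers a contrast of AUC 0.95 for the EHG against 0.70 for standard diagnostics, using a "two-sided *z*-test at a significance level of 0.05". Its 40/60 split rests on the statement "Approximately 40% of these patients delivered within 7 days". No other window has a stated event share.

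**The concern.** With four windows, two parameters, no lead and 0.05 for each test, the plan does not say which result decides whether CV discriminates. If CV carried no information about time to delivery, the chance of at least one nominally significant primary result would exceed 5%, and nothing in the text would prevent that result from being reported as the primary finding.

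The disagreement between sections makes this worse. A reader cannot tell whether the study stands or falls on a difference in group means, on accuracy at a given window, or on an AUC difference between two diagnostic methods.

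**Working it through.** **Inputs from the protocol article.** N = 100, 40% delivered by 7 days and a two-sided 0.05 for the powered test (Sample size); four windows and two parameters (Study parameters/Endpoints); 0.05 for all tests and a t-test for amplitude (Statistical analysis).

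**Assumed inputs.** The shares delivered by 1, 2 and 14 days are not given, so a range is used. The correlation between amplitude and angle is not given, so 0 and 0.5 are used.

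**The plan's own figures.** A single two-sided t-test at 7 days (40 versus 60 women) gives a simulated error of 4.9%, which matches the stated 0.05. The stated 82% power (7 versus 11 patients) cannot be confirmed, because the correlation between the two diagnostic tests is not given. It is about 40% at zero correlation (21–69% depending on the null variance used), and about 82% appears at a correlation near 0.8 under some variance choices. That figure belongs to the AUC contrast and does not enter the calculation below.

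**Reference if the tests were independent.** Error = 1 − (1 − 0.05)^k.

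- k = 4: 1 − 0.95^4 = 18.5%
- k = 8: 1 − 0.95^8 = 33.7%

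The windows are nested: a woman delivering within 1 day also counts at 2, 7 and 14 days. The tests are therefore positively correlated and these values are only upper references.

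**Simulation with nested windows.** 20,000 to 40,000 trials of 100 women, values independent of time to delivery, two-sided pooled t-test at each window, counting trials with any p < 0.05. Angle is represented by a second normal variable tested in the same way.

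| Delivered by 1/2/7/14 days | Amplitude, 4 tests | Both, correlation 0 | Both, correlation 0.5 |
|---|---|---|---|
| 30/35/40/45% | 10.4% | 19.8% | 17.7% |
| 15/25/40/50% | 13.5% | 25.2% | 23.6% |
| 5/15/40/60% | 15.8% | 29.0% | 27.5% |

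Amplitude alone runs at about 10–16%, two to three times 0.05. With angle included the rate is about 18–29%, or 3.5 to 6 times 0.05.

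**Effect of the possible remedies.**

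- One window and one parameter: 4.9%.
- One window with both parameters unadjusted: 9.7%.
- Bonferroni over eight tests (0.05/8 = 0.00625 each): 3.0–4.3%, at a price in power. The detectable standardised difference at 80% power with 40 versus 60 is (z for alpha + z for power) × √(1/40 + 1/60). It rises from 0.57 at 0.05 to 0.73 at 0.00625, and power at 0.57 falls from 80% to about 53%.

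**The case against.** The strongest reply is that this is an observational accuracy study looking at one hypothesis over several horizons, that a condensed article commonly leaves multiplicity to an analysis plan, and that no rule is stated under which any single significant result counts as success. The last point is true: the error rate above is what the plan permits, not a success rule it declares. The appeal to an unseen analysis plan is weaker, because the article is not silent. It sets 0.05 for all tests, and it names a primary outcome. Reporting the AUC does not remove the problem either: it avoids choosing a CV threshold, but a separate AUC is still needed for each delivery window.

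Several stronger readings are tempting and are not supported:

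- **Ten primary tests.** A reader might multiply the Abstract's five windows by two parameters. The five windows belong to sensitivity, specificity and AUC, for which the Statistical analysis section names no test. That count merges two different sets of endpoints.
- **An error rate of 34% or more.** This treats nested windows as independent.
- **The higher range as established.** No test is named for angle, which is a directional quantity, so the 18–29% is conditional on its being tested at 0.05.
- **The powered 0.05 is broken.** That alpha belongs to the AUC contrast, not to the comparison of group means. Nor was the study sized for amplitude at 7 days: only the 40/60 split comes from that window. The increase to 100 was partly meant to allow for other splits.

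**Conclusion.** The concern holds. Amplitude at four windows, each at 0.05 and with no lead, carries about a 10–16% chance of a false-positive primary result. If angle is tested in the same way, the figure is about 18–29%. Both ranges rest on the assumed event shares at 1, 2 and 14 days, and the second also on a correlation of 0 to 0.5 between the parameters. That the rate exceeds 5% does not depend on the particular shares tried: it stays at about twice 0.05 even when the windows lie close together.

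Separately, and without any assumption, the article gives three different accounts of the main analysis and two different lists of windows.

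**What to change.** 1. Name one primary analysis at the 7-day window, the only one with a stated event share. It can be the AUC comparison of EHG with standard diagnostics that the Sample size section powers, or the comparison of CV amplitude between groups. If amplitude is chosen, state that the sample size was not calculated for it.
2. Make the other windows and CV angle secondary or exploratory, reported as estimates with confidence intervals and without claims of significance. Limit the 0.05 rule to the primary test accordingly.
3. Use the same main endpoint and the same list of windows in the Abstract, the endpoint section and the Discussion, either removing the 4-day window or adding it everywhere.

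The cost is wording. No extra patients are needed, and the power loss of a Bonferroni correction is avoided. The sponsor gives up claiming success on a 1-, 2- or 14-day result, or on angle, alone.

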## Discussion

The study aims to evaluate CV analysis of the EHG as clinical tool for the diagnosis of imminent preterm delivery. In an observational cohort study the EHG will be recorded in patients admitted for threatened preterm labor. The CV will be estimated in the EHG using a fully automated analysis. This automated approach entails a novel automatic selection of contractions based on the eIUP and automatic delay estimation. The diagnostic accuracy will be expressed in terms of sensitivity, specificity and area under the ROC curve for delivery within 1,2,7, and 14 days from the measurement.

Similar to [5], part of the patients will already be treated with tocolytics at the time of the measurement. This could influence the amount of contractions and possibly the CV as well. Using logistic regression, the administration of tocolytics will be tested as possible confounding factor. The EHG CV analysis will be evaluated as diagnostic tool for predicting imminent spontaneous preterm delivery. Although it is not a common scenario in patients admitted for threatened preterm labor, patients within the labor group in which labor is induced will not be included in the final analysis.

Perhaps the biggest challenge and also an essential step in accurate estimation of the CV is recognizing contractions amongst noise and artifacts in the EHG. Different from term patients in labor, preterm patients admitted for threatened preterm labor have mostly an irregular pattern of uterine contractions of a varying frequency as well as duration. Therefore, the detection algorithm cannot assume a regular pattern and fixed duration. Furthermore an external tocodynamometer can fail to show contractions in some patients [40,41]. Therefore, for use as independent clinical tool, the EHG CV analysis cannot rely on the external tocodynamometer as reference. Hence the analysis will be mainly based on the electrical signal recorded on the skin.

Our methods will entail filtering in a narrow frequency band (0,3 – 0,8 Hz) in order to suppress signals other than uterine activity, including (abdominal) striated muscle activity and the maternal electrocardiogram. The eIUP will be used in order to distinguish uterine activity from the background noise. Visual review of the data is envisaged to evaluate the performance of the automatic algorithm.

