Unlike in our previous work, the time delays between channels will be estimated using cross-correlation. The maximum likelihood method previously proposed, will not be used for this study since it is more suitable when more electrodes are used. Furthermore, given the need for a short time window, no frequency based method can be applied on account of loss of resolution. In addition, it would also increase the complexity and therefore computing time of the algorithm, impeding the use as clinical tool. Using cross-correlation, the resolution in time is dictated by the sampling frequency of the recording and therefore we will use a relatively high sampling frequency of 1000Hz.

The four electrodes of the patch enable the CV vector to be estimated in all the possible directions along the abdominal plane. By using different triangles of electrodes depending on the direction of propagation, the problem of action potentials originating from within the electrodes is mostly solved. Since the dimensions of the electrodes patch are relatively small compared to the whole uterine surface, planar wave propagation will be assumed for the calculation of the CV vector. To explore uterine propagation patterns in detail, an electrode grid containing more electrodes and of a relatively big size would be needed. However this falls beyond the scope of this project, which has the objective to test a clinical application for distinguishing low from high CVs in order to timely recognize imminent preterm labor.

To summarize, in this study the diagnostic accuracy of EHG CV analysis will be evaluated for detecting preterm labor. By employing a fully automated analysis of the EHG without the use of external reference signals, this project aims to make the next step towards introducing the EHG CV analysis as clinical tool.

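### The body names a labor v non-labor difference in conduction velocity as the primary outcome, while the abstract, the aim and the sample size rest on diagnostic accuracy

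*Protocol article*

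**What the plan says.** The protocol article states its main endpoint in two ways.

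- **Study parameters/Endpoints:** "As primary outcome the EHG parameters will be compared between these groups in terms of amplitude and angle of the CV". The cervical length comparison is then called secondary. Sensitivity and specificity follow, and finally "the area under the curve of the receiver operating characteristics will be determined". None of these accuracy measures is labelled primary or secondary.
- **Abstract, Methods/Design:** "The main study endpoints will be sensitivity, specificity, and area under the ROC curve". The abstract also mentions comparing average CV and cervical length between the groups, but does not make that a main endpoint.

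Three other statements bear on which is meant.

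- **Discussion, aim:** "in this study the diagnostic accuracy of EHG CV analysis will be evaluated for detecting preterm labor". The same section adds: "The diagnostic accuracy will be expressed in terms of sensitivity, specificity and area under the ROC curve for delivery within" 1, 2, 7 and 14 days.
- **Sample size:** the calculation is made "assuming an area under the ROC curve of 0,95 for EHG CV analysis and 0,70 for the standard diagnostics". It takes about 40% of women as delivering within 7 days and arrives at 100 women.
- **Statistical analysis:** the only between-group test described for CV is an independent samples t-test on amplitude, with alpha 0.05 for every test.

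**The concern.** A primary outcome fixes in advance which result governs the conclusion. Here the body fixes a difference between groups, while the abstract fixes accuracy. A reader cannot tell which one decides the study, and the choice could be made after both are known.

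The two also answer different questions. A significant t-test shows that mean amplitude differs between women who deliver soon and those who do not. It does not show how well CV separates individual women, nor whether it does so better than existing tests. At 100 women, a mean difference too small to be useful for diagnosis can be significant. The body's primary outcome could therefore come out positive for a test that discriminates no better than the standard diagnostics the study was sized against.

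**Working it through.** **The plan's own figure.** The Sample size section gives 82% power for AUC 0.95 v 0.70 with 7 positive and 11 negative women. Hanley-McNeil standard errors at 7/11 are 0.0616 (AUC 0.95) and 0.1332 (AUC 0.70). A one-sample z-test with 0.95 as the null value gives Φ((0.25 − 1.96 × 0.0616)/0.1332) = 83.4%; the Obuchowski rating-scale variance gives 82.7%. More natural settings give less: 43% with 0.70 as the null value, and 40% for two uncorrelated ROC curves (both Hanley-McNeil). A paired comparison reaches 81.9% only at an unstated correlation of about 0.85. The present point does not depend on this figure. What matters is that the calculation concerns AUC and not a mean difference.

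**Inputs for the t-test.** N = 100 and a 40/60 split at 7 days (Sample size); alpha 0.05 (Statistical analysis). Assumed: two-sided test, all 100 women evaluable, CV amplitude normal with equal variances.

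**Smallest significant difference at 40/60.**
- Critical t on 98 df = 1.984.
- √(1/40 + 1/60) = 0.2041.
- Standardised difference d = 1.984 × 0.2041 = 0.405.
- AUC = Φ(d/√2) = Φ(0.286) = 0.613.
- Sensitivity = specificity at the midpoint = Φ(d/2) = Φ(0.203) = 58%.
- Hanley-McNeil SE of that AUC = 0.058, so the 95% CI is about 0.50 to 0.73.

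**Chance of a significant t-test when the true AUC is 0.70.** d = √2 × Φ⁻¹(0.70) = 0.742. At 40/60 the noncentrality is 0.742/0.2041 = 3.63, and noncentral-t power is 95%. At a true AUC of 0.65 (d = 0.545) power is 75%.

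**Other splits.** The protocol gives the labor share for 7 days only, so the other rows are assumptions that show the range.

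| Split | √(1/n₁+1/n₂) | Smallest significant d | AUC at that d | Power at true AUC 0.65 | Power at true AUC 0.70 |
|---|---|---|---|---|---|
| 40/60 | 0.204 | 0.405 | 0.613 | 75% | 95% |
| 30/70 | 0.218 | 0.433 | 0.620 | 70% | 92% |
| 20/80 | 0.250 | 0.496 | 0.637 | 58% | 84% |
| 10/90 | 0.333 | 0.661 | 0.680 | 37% | 60% |

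With 80 evaluable women at 32/48 the threshold is 0.626. It stays below 0.70 in all of these cases.

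**What an accuracy endpoint would require.** For a paired comparison against AUC 0.70 at 40/60 (Hanley-McNeil, correlation assumed between 0 and 0.6), 80% power needs a CV AUC of about 0.89 (r = 0) to 0.83 (r = 0.6). Power for the plan's own 0.95 v 0.70 is about 99% or more. The t-test already has 80% power at a true AUC of about 0.66.

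**The case against.** Several points on the other side stand.

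- **Accuracy is still planned.** Sensitivity, specificity and AUC appear in the Endpoints section and the Discussion, and sensitivity and specificity again under Statistical analysis. A reader might infer that the study as a whole cannot answer its diagnostic question. The text does not support that: the limit applies to the outcome labelled primary.
- **The overlap is considerable.** The abstract also plans the group comparison, and the body attaches the word secondary to the cervical length comparison. The accuracy measures are unlabelled, not expressly demoted.
- **No success rule is tied to the t-test.** A reader might infer that the sponsor would declare CV a clinical tool on a significant mean difference. The article says only that CV analysis will be evaluated, as a step towards clinical use. The AUC would be reported beside the p-value.
- **The 0.61 is one case.** It is the smallest observed AUC that reaches significance at one split, not an effect detected reliably: at a true AUC of 0.61 the chance of significance is about 48%. With smaller labor groups the threshold rises, and removing induced women from the labor group, as the Discussion plans, would reduce the numbers.
- **A fixed 0.70 is a poor benchmark.** It follows a Bishop score result of 0.72 in another study, whereas the comparator planned here is cervical length in the same cohort.

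None of this removes the contradiction. It cannot simply be left to an analysis plan, because the protocol article already states a primary outcome, and that statement conflicts with its own abstract and sample size.

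**Conclusion.** The point holds as a contradiction between endpoint statements. The body's primary outcome differs from the abstract's main endpoints and from the quantity on which the study was sized, and it does not by itself measure diagnostic accuracy. Under the stated assumptions, the t-test turns significant at an observed AUC of 0.61 to 0.68 across splits from 40/60 to 10/90. A CV test only as good as the assumed standard diagnostics would give a significant difference 95% of the time at 40/60, falling to 60% at 10/90.

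This should be fixed. It does not invalidate the study, since the accuracy measures are already planned and only the hierarchy among them is wrong.

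**What to change.** In Study parameters/Endpoints:

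1. Name as primary the AUC of per-patient CV amplitude for delivery within 7 days, with its 95% CI. This matches the abstract, and 7 days is the interval the Sample size section uses. Naming one cutoff matters; otherwise several AUCs compete.
2. Make the group comparison of amplitude and angle secondary, together with the other cutoffs.
3. Base any claim of improvement over standard diagnostics on the paired AUC difference between CV and cervical length, in women who have both. Under Inclusion and measurement, cervical length is taken as a standard test with intact membranes, so this subset may be smaller than 100; its size should be reported. Neither the t-test nor a fixed external 0.70 should carry that claim.

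**Cost.** Mostly wording. The AUC is already planned; its confidence interval and the paired comparison need a little extra analysis. A small but significant mean difference would no longer count as a positive primary result. The paired comparison also asks more of CV: with all 100 women at 40/60 and a comparator AUC of 0.70, 80% power needs a CV AUC of roughly 0.83 to 0.89, depending on the correlation, and more if fewer women have both measurements.
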